## Abstract

**Background:**

Obesity and type 2 diabetes mellitus (T2DM) are associated with accelerated brain atrophy, white matter microstructural disruption, and resting-state functional network dysconnectivity in elderly adults, driven by converging vascular, neuroinflammatory, and insulin-resistance mechanisms. Yoga is a recognized mind-body intervention with documented benefits for glycaemic control, vascular health, and neurocognitive function; however, no study has yet employed multimodal MR neuroimaging to systematically characterize these brain alterations in an elderly obese-diabetic population or to evaluate yoga-induced neuroplasticity within this cohort.

**Methods:**

This three-phase, prospective protocol will be conducted at Kasturba Hospital and the Center for Integrative Medicine and Research, Manipal Academy of Higher Education, Manipal, India. Phase 1 is a case-control study (n = 80; 40 obese-diabetic, 40 obese-non-diabetic; age 60–80 years) employing carotid Doppler ultrasonography, T1-weighted voxel-based morphometry and region-of-interest segmentation (SPM12/CAT12/AAL3), diffusion tensor imaging with ROI-based tractography (ExploreDTI), and resting-state fMRI (CONN toolbox), alongside the Eriksen Flanker and N-Back cognitive tasks. Phase 2 involves the systematic development and expert content-validation of a structured, AYUSH-compliant yoga module tailored for elderly obese-diabetic adults. Phase 3 applies the validated module in a 6-month pre-post intervention, with objective adherence monitoring via triaxial accelerometry and repeat of the full Phase 1 neuroimaging and cognitive battery.

**Discussion:**

This protocol addresses a critical gap in the yoga-neuroimaging literature by providing a multimodal, multi-phase framework to characterize neurovascular disease burden and evaluate structured yoga as a neurobiologically informed lifestyle intervention in a high-risk elderly population. Findings will inform AYUSH clinical guidelines, geriatric NCD prevention programs, and future randomized controlled trials.

## 1. Introduction

The global burden of non-communicable diseases (NCDs) has reached unprecedented levels, with obesity and type 2 diabetes mellitus (T2DM) constituting two of the most consequential metabolic disorders of the twenty-first century. According to the World Health Organization, the worldwide prevalence of obesity has nearly doubled since 1990, with more than 890 million adults classified as obese in 2022.
^
1
^ Concurrently, the International Diabetes Federation estimates that approximately 537 million adults were living with diabetes in 2021, a figure projected to rise to 783 million by 2045.
^
2
^ These epidemiological trends are particularly alarming in the elderly population, among whom both conditions frequently co-occur and exert synergistic deleterious effects on systemic health. In India, rapid urbanization, sedentary lifestyles, and dietary transitions have accelerated the prevalence of these metabolic comorbidities, making them priority targets under the National Program for Prevention and Control of Cancer, Diabetes, Cardiovascular Diseases, and Stroke.
^
3
^

Beyond their well-established cardiovascular and metabolic sequelae, obesity and T2DM exert profound adverse effects on brain structure and function. Structural neuroimaging studies have consistently demonstrated accelerated brain atrophy, reduced grey matter volume, and compromised white matter integrity in individuals with obesity and T2DM relative to metabolically healthy controls.
^
4,
5
^ Particularly vulnerable regions include the hippocampus, prefrontal cortex, and parietal association areas, structures critically involved in memory consolidation, executive function, and visuospatial processing.
^
6
^ Diffusion tensor imaging (DTI) studies further reveal microstructural white matter disruption, evidenced by reduced fractional anisotropy (FA) and elevated mean diffusivity (MD) in major fiber tracts, consistent with demyelination and axonal loss.
^
7
^ These neuroanatomical alterations are accompanied by functional connectivity changes detectable on resting-state functional MRI, pointing to disrupted default mode and frontoparietal networks in metabolically compromised individuals.
^
8
^ Taken together, this body of evidence positions obesity associated T2DM as a significant and modifiable risk factor for accelerated neurocognitive aging.

The mechanisms underlying brain alterations in obese-diabetic individuals are multifactorial, but vascular dysfunction plays a central and unifying role. Chronic hyperglycemia and dyslipidemia promote endothelial dysfunction, arterial stiffness, and impaired cerebrovascular autoregulation, collectively reducing cerebral perfusion and predisposing the brain to ischaemic injury.
^
9
^ Carotid artery intima-media thickness (cIMT), a validated surrogate marker of subclinical atherosclerosis, is significantly elevated in individuals with T2DM and is independently associated with reduced hippocampal volume and cognitive decline.
^
10
^ Furthermore, adipose tissue-derived proinflammatory cytokines, including interleukin-6 (IL-6) and tumor necrosis factor-alpha (TNF-α), disrupt the blood-brain barrier, foster neuroinflammation, and impair insulin signaling within the central nervous system, thereby compounding structural brain damage.
^
11
^ Insulin resistance in the brain has been specifically linked to tau hyperphosphorylation and amyloid-beta accumulation, suggesting a mechanistic overlap between T2DM and Alzheimer’s disease pathology.
^
12
^ Understanding these vascular-neural interactions is therefore critical to identifying therapeutic windows for intervention in elderly individuals with metabolic comorbidities.

Cognitive impairment is an important but frequently underrecognized complication of combined obesity and T2DM in the elderly. Longitudinal cohort studies indicate that individuals with both conditions face a substantially elevated risk of developing mild cognitive impairment (MCI) and dementia compared to those with either condition alone, suggesting additive or synergistic pathophysiology.
^
13
^ Domains most consistently affected include episodic memory, processing speed, executive function, and attentional control, all of which have significant implications for functional independence, quality of life, and adherence to self-management behaviors in this population.
^
14
^ Neuropsychological assessments such as the N-Back memory task and the Eriksen Flanker test provide sensitive and ecologically valid measures of working memory capacity and attentional inhibition, respectively, and have been employed in neuroimaging paradigms to establish structure-function relationships in metabolically at-risk cohorts.
^
15
^ The use of such cognitive probes in conjunction with multimodal MRI, therefore, offers a comprehensive framework for characterizing neurocognitive vulnerability in elderly adults with obesity and T2DM.

Yoga, a traditional Indian mind-body practice encompassing physical postures (asanas), breath regulation (pranayama), and meditative techniques, has attracted growing scientific interest as a holistic lifestyle intervention for metabolic and neurological health. A robust evidence base now supports the efficacy of yoga in improving glycaemic control, reducing body mass index (BMI), lowering systolic blood pressure, and attenuating inflammatory biomarkers in individuals with T2DM and obesity.
^
16,
17
^ Yoga has been shown to enhance vagal tone and modulate the hypothalamic-pituitary-adrenal (HPA) axis, thereby reducing allostatic load and counteracting the sympathoadrenal overactivation characteristic of metabolic syndrome.
^
18
^ Regarding brain health, preliminary neuroimaging studies have reported that yoga is associated with increases in cortical thickness, hippocampal volume, and grey matter density in regular practitioners compared to non-practitioners, accompanied by improvements in cognitive performance and emotional regulation.
^
19,
20
^ These structural adaptations are thought to be mediated in part by yoga-induced elevations in brain-derived neurotrophic factor (BDNF) and insulin-like growth factor-1 (IGF-1), both of which promote neuroplasticity and neurogenesis in the hippocampal dentate gyrus.
^
21
^

Despite these promising findings, significant gaps persist in the literature. First, most yoga intervention studies have been conducted in younger or otherwise healthy populations, with limited generalization to elderly adults burdened with metabolic comorbidities.
^
22
^ Second, existing neuroimaging investigations of yoga have largely relied on cross-sectional designs, precluding causal inference regarding the direction and magnitude of yoga-induced brain changes.
^
23
^ Third, to date, no studies have employed a multi-sequence MRI protocol combining volumetric morphometry, DTI, and resting-state fMRI to concurrently characterize structural, microstructural, and functional brain network adaptations to yoga in elderly obese-diabetic individuals. Fourth, there remains a lack of culturally validated, evidence-based, structured yoga modules specifically tailored to the physiological constraints and comorbidity profiles of this demographic, constituting a critical barrier to clinical translation.
^
24
^ Addressing these gaps requires a rigorous, prospective, and multimodal investigation.

## 2. Protocol

### 2.1 Study design

This study is a three-phase, prospective investigation integrating a cross-sectional case-control design (Phase 1), an instrument development and validation phase (Phase 2), and a pre-post interventional design (Phase 3). The protocol was approved by the Indian Council of Medical Research (ICMR) under the Call for Investigator-Initiated Research Proposals for Small Extramural Grants (Priority Area: NCD Risk Factors — Diabetes; Aging and Elderly Health).

### 2.2 Study setting

All neuroimaging data (MRI and Doppler) will be acquired at the Department of Radiodiagnosis and Imaging, Kasturba Hospital, Manipal, using a 3-Tesla United Imaging uMR 780 MRI system. Cognitive assessments will be conducted in a dedicated, distraction-free testing room in the same department. The yoga module development and validation (Phase 2) will be carried out at the Division of Yoga, Centre for Integrative Medicine and Research (CIMR), Manipal. Physical activity data will be captured using accelerometers.

### 2.3 Phase 1

**2.3.1 Objectives**

The primary objective of Phase 1 is to determine and compare vascular, structural, and functional brain changes, along with alterations in cognitive function, between obese elderly adults with T2DM and those without T2DM using multimodal MR neuroimaging.

**2.3.2 Study design**

Case-control study.

**2.3.3 Inclusion criteria**
•Age 60–80 years, both sexes.•Clinical diagnosis of type 2 diabetes mellitus for the obese-diabetic group.•Body mass index (BMI) ≥ 25 kg/m
^2^ as per Asia-Pacific guidelines for obesity classification.
^
25
^
•Able to provide written informed consent independently or through a legally authorized representative.

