**2.3.4 Exclusion criteria**
•Presence of neurological or psychiatric conditions known to affect brain morphology or cognitive function (e.g., Parkinson’s disease, major depressive disorder, schizophrenia, prior stroke or traumatic brain injury).•History of neurodegenerative disease (e.g., Alzheimer’s disease, vascular dementia).•Type 1 diabetes mellitus or secondary forms of diabetes.•Active malignancy or any systemic illness likely to confound neuroimaging or cognitive assessments.•Contraindications to MRI (metallic implants, claustrophobia, cardiac pacemakers).•Current or recent (within 6 months) regular yoga practice (≥ 2 sessions per week).•Severe hearing or visual impairment precluding cognitive testing.

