**2.3.5 Sample size**

Sample size was estimated using G*Power 3.1 software. A multivariate analysis of variance (MANOVA) power analysis was performed with an assumed medium effect size (f
^2^ = 0.25), a significance level of α = 0.05, and a desired statistical power of 0.80. This yielded a minimum total sample of 80 participants. Accounting for anticipated attrition and protocol deviations, 40 participants will be recruited to each group (obese-diabetic and obese-non-diabetic), yielding a total of 80 participants for Phase 1.

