**2.3.6.2 Anthropometric and metabolic measurements**

Height will be measured to the nearest 0.1 cm using a calibrated stadiometer, and body weight will be recorded to the nearest 0.1 kg using a digital weighing scale, with participants barefoot and in light clothing. BMI will be calculated as weight (kg) divided by height squared (m
^2^). Waist circumference will be measured at the midpoint between the lowest rib and the iliac crest. Fasting blood glucose and HbA1c will be recorded from participants’ clinical laboratory reports.

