**2.5.8 Post-Intervention assessment**

Following the 6-month intervention period, all participants will undergo a complete repeat of the neuroimaging protocol and cognitive assessments as described in Phase 1. Physical activity, anthropometric, and metabolic measurements will also be repeated using identical procedures and equipment.

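### The obese-non-diabetic group has no glycaemic criterion, so people with undiagnosed diabetes can enter the Phase 1 controls and pull true group differences toward the null

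*Protocol article*

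**What the plan says.** Section 2.3.1 makes diabetes status the exposure of Phase 1; the comparison is "between obese elderly adults with T2DM and those without T2DM using multimodal MR neuroimaging". Section 2.3.3 lists the inclusion criteria, and its single diabetes criterion is "Clinical diagnosis of type 2 diabetes mellitus for the obese-diabetic group". No inclusion criterion is specific to the other group. Among the exclusions in section 2.3.4, the diabetes item is "Type 1 diabetes mellitus or secondary forms of diabetes", which does not cover unrecognised T2DM.

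Section 2.3.6.2 provides the data that could verify status: "Fasting blood glucose and HbA1c will be recorded from participants’ clinical laboratory reports". It sets no threshold, no limit on the age of a report and no use in assigning or confirming group.

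Section 2.3.5 plans 40 participants per group. Section 2.3.6.7 compares the groups by t-test or Mann-Whitney test at two-sided 0.05. The regression models there adjust for age, sex, education and physical activity. Metabolic indices appear only in the association analyses.

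**The concern.** Every Phase 1 group contrast uses the same label, and on the listed rules that label rests on a diagnosis having been made. Where no diagnosis has been made, nothing listed distinguishes a person without diabetes from one whose diabetes is unrecognised. The controls are obese and aged 60–80, and the protocol's introduction says that obesity and diabetes frequently occur together in older people.

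A control who is in fact diabetic moves the control mean toward the case mean, so a real difference is underestimated and is harder to detect. Section 2.3.5 leaves no reserve against this: the calculated minimum is 80 and planned recruitment is also 80. An undated report adds a second weakness, because it may not describe the participant's status at the time of the scan.

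**Working it through.** **Inputs from the protocol.** 40 per group, α = 0.05, target power 0.80, f² = 0.25 for a MANOVA (section 2.3.5); two-sided t-test (section 2.3.6.7).

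**Inputs assumed.** The share c of controls with unrecognised diabetes is taken as 5–20%. The fraction h of the full diabetic effect that they carry is taken as 1 or 0.5. Neither figure is in the documents.

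**The plan's own figure.** For a two-group MANOVA with p responses, df1 = p, df2 = N − p − 1 and noncentrality = N·f². With f² = 0.25 and 80% power, the required N is 34 for p = 1, 53 for p = 4, 78 for p = 11 and 81 for p = 12. The stated 80 therefore corresponds to about 11 or 12 responses. The article does not state p, so the planning value cannot be turned into one effect per outcome. I use two starting points instead:

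- d = 0.634, the difference that 40 per group detects with 80% power in a two-sided 0.05 t-test. It is illustrative and solved backwards from the power.
- d = 1.0, which is what f² = 0.25 means for a single outcome in two equal groups: f = √0.25 = 0.5 and d = 2f = 1.0.

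**Dilution model.** With the within-group SD set to 1:

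- observed difference = d(1 − c·h)
- control variance = 1 + c(1 − c)(h·d)²
- pooled SD = √[(1 + control variance)/2]
- observed d = observed difference / pooled SD
- power from the noncentral t distribution with 78 df and noncentrality = observed d × √(40/2)

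Example with d = 0.634, c = 0.10, h = 1: the difference is 0.634 × 0.90 = 0.571. The control variance is 1 + 0.09 × 0.402 = 1.036 and the pooled SD is 1.009. The observed d is 0.571/1.009 = 0.566, and power is 70.5%.

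| c (assumed) | d = 0.634, h = 1: observed d | Power | d = 0.634, h = 0.5: power | d = 1.0, h = 1: power |
|---|---|---|---|---|
| 0% | 0.634 | 80% | 80% | 99.3% |
| 5% | 0.600 | 75.5% | 78% | 98.6% |
| 10% | 0.566 | 70.5% | 76% | 97.3% |
| 15% | 0.532 | 65% | 73% | 95% |
| 20% | 0.499 | 60% | 71% | 92.5% |

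**Chance that it happens at all.** The probability of at least one misclassified control among 40 is 1 − (1 − c)^40. At c = 2% it is 55%, and at c = 5% it is 87%.

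**The case against.** The strongest reply is that the comparison group is defined, as people without T2DM, and that a journal article may leave the operational rule to a fuller protocol. Staff who record HbA1c would see a diabetic-range value, and keeping that person as a control would conflict with the stated objective. This stands in part: no section says that such a person is kept, and a reader should not infer that the protocol intends it. But the phrase states an aim and gives no way to establish status. The article also prints its eligibility lists with thresholds, such as those for BMI and recent yoga practice. Group definition is an eligibility matter that an analysis plan cannot repair after recruitment.

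Three stronger readings are tempting, and the documents do not support them.

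- **That undiagnosed diabetics do enter and dilute every contrast.** No rate is given, so entry is possible but not shown. An outcome with no true group difference is not diluted.
- **That power will fall to 60%.** That figure needs 20% contamination, an effect of exactly d = 0.634, and unrecognised cases as affected as diagnosed ones. Milder cases or a larger true effect cost much less.
- **That the 6-month metabolic change is compromised.** Section 2.5.8 says "Physical activity, anthropometric, and metabolic measurements will also be repeated using identical procedures and equipment", and reusing an old report would not be a repeat. Metabolic change is not among the Phase 3 primary or secondary outcomes. This is a side issue.

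It is also fair to say that the bias runs toward the null, so it does not create false group differences, and that status can be checked later wherever a usable report exists.

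**Conclusion.** The point holds as a weakness in how the exposure is fixed. The listed rules allow misclassified controls, and the values that could detect them are collected without being put to that use. The direction of the effect is clear for any outcome with a true difference, but its size is not known.

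In the illustrative case of d = 0.634, an assumed 5–20% contamination lowers power from 80% to about 75–60%. This is an upper bound for a given rate, provided that unrecognised cases are no more affected than diagnosed ones. At half the effect the range is about 78–71%. At d = 1.0 power stays at 92.5% or more throughout. The change is worth making before enrolment, but the conclusion does not go as far as saying that Phase 1 will fail.

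**What to change.** Add a definition of the obese-non-diabetic group to section 2.3.3: no diabetes diagnosis, no glucose-lowering treatment, and recorded HbA1c and fasting glucose below diagnostic cut-offs that the sponsor names. The values should come from reports dated within a window of the MRI that the sponsor also fixes. State that participants above the cut-off are not counted as controls. Where no report falls within the window, flag the participant and repeat the Phase 1 primary contrasts without the unconfirmed controls, as a sensitivity analysis.

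The cost is an eligibility amendment. A few screened controls would be replaced, and some will lack a current report, so either one is obtained or the participant stays unconfirmed. The planned 40 per group need not change. The Data Availability section says that no participant data had been collected at publication, so the change is cheap if made before enrolment. After recruitment, a control with no usable report cannot be verified from the recorded data.

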**2.3.4 Exclusion criteria**
•Presence of neurological or psychiatric conditions known to affect brain morphology or cognitive function (e.g., Parkinson’s disease, major depressive disorder, schizophrenia, prior stroke or traumatic brain injury).•History of neurodegenerative disease (e.g., Alzheimer’s disease, vascular dementia).•Type 1 diabetes mellitus or secondary forms of diabetes.•Active malignancy or any systemic illness likely to confound neuroimaging or cognitive assessments.•Contraindications to MRI (metallic implants, claustrophobia, cardiac pacemakers).•Current or recent (within 6 months) regular yoga practice (≥ 2 sessions per week).•Severe hearing or visual impairment precluding cognitive testing.

**2.3.5 Sample size**

Sample size was estimated using G*Power 3.1 software. A multivariate analysis of variance (MANOVA) power analysis was performed with an assumed medium effect size (f
^2^ = 0.25), a significance level of α = 0.05, and a desired statistical power of 0.80. This yielded a minimum total sample of 80 participants. Accounting for anticipated attrition and protocol deviations, 40 participants will be recruited to each group (obese-diabetic and obese-non-diabetic), yielding a total of 80 participants for Phase 1.

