**2.3.6.7 Statistical analysis**

All statistical analyses will be performed using Jamovi. Demographic and clinical characteristics will be summarised using descriptive statistics: mean ± standard deviation (SD) for normally distributed continuous variables; median and interquartile range (IQR) for skewed data; and frequencies with percentages for categorical variables. Normality will be assessed using the Shapiro-Wilk test. Group differences in neuroimaging and cognitive outcomes will be examined using independent-samples t-tests or Mann-Whitney U tests, as appropriate. A two-way ANOVA will be used to investigate interactions between group and sex or age; a nonparametric alternative (Kruskal-Walli’s test with Dunn’s post hoc correction) will be applied when distributional assumptions are violated. Associations between neuroimaging metrics, vascular parameters, metabolic indices, and cognitive performance will be explored using Pearson’s or Spearman’s correlation coefficients and multiple linear regression models, adjusting for age, sex, years of education, and physical activity level. A significance threshold of p < 0.05 (two-tailed) will be applied throughout.

### 2.4 Phase 2

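### The Phase 1 sample-size paragraph adds nothing for attrition, calls f² = 0.25 medium, and attaches its 80% power to a MANOVA that the analysis section does not plan

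*Protocol article*

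**What the plan says.** Section 2.3.5 (Sample size) of the protocol article describes a G*Power calculation: "A multivariate analysis of variance (MANOVA) power analysis was performed with an assumed medium effect size", written as f² = 0.25, with "a significance level of α = 0.05" and "a desired statistical power of 0.80". The result and the recruitment target follow directly: "This yielded a minimum total sample of 80 participants. Accounting for anticipated attrition and protocol deviations, 40 participants will be recruited to each group". The section gives no attrition rate.

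Section 2.3.6.7 (Statistical analysis) sets out the Phase 1 comparison: "Group differences in neuroimaging and cognitive outcomes will be examined using independent-samples t-tests or Mann-Whitney U tests". It adds a two-way ANOVA for interactions with sex or age, correlations and multiple linear regression, and closes with "A significance threshold of p < 0.05 (two-tailed) will be applied throughout". No MANOVA is listed there. Section 2.5.10, for Phase 3, lists paired tests, mixed-effects models, partial correlations and multivariate regression, and no MANOVA either.

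**The concern.** The paragraph is the only justification for the size of Phase 1, and three of its statements do not agree with their own numbers or with the analysis section.

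- **Attrition.** The minimum and the recruitment target are the same number, although the text says that losses have been allowed for.
- **Effect size.** The label and the value describe different effects. A reader who trusts the label believes that the study is sized for a modest difference. A reader who trusts the number sees a difference of a full standard deviation on one outcome.
- **Test.** The power belongs to a multivariate test, but the conclusions will come from one univariate test per outcome.

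What is at stake is how Phase 1 results are read. If the paper reports 80% power for a medium effect, a non-significant result could be taken as evidence against a difference of about half a standard deviation. The planned test does not have that sensitivity.

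**Working it through.** **Inputs.** From section 2.3.5: f² = 0.25, alpha 0.05, power 0.80, minimum 80, recruitment 40 + 40. From section 2.3.6.7: two-sided 0.05, independent-samples t-test. Assumed here, because the document gives no rate: losses of 10% and 20%.

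**1. The plan's own figure.** For a two-group MANOVA with p response variables, power follows a noncentral F with df₁ = p, df₂ = N − p − 1 and λ = N·f². At f² = 0.25 and 80% power, the minimum N is:

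| p | 1 | 5 | 10 | 11 | 12 |
|---|---|---|---|---|---|
| N | 34 | 58 | 75 | 78 | 81 |

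The article does not state p. A total of 80 fits about 11 responses (78 needed; power 81.7% at N = 80). The figure is therefore attainable and is not treated as an arithmetic error.

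**2. Attrition.** Recruited minus minimum = (40 + 40) − 80 = 0. To keep 80 evaluable, recruitment would have to be 80/(1 − loss): 80/0.90 = 88.9, so 89, at 10% loss; 80/0.80 = 100 at 20% loss.

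**3. Effect-size scale.** f = √0.25 = 0.50. For two equal groups and one outcome, d = 2f = 1.0. The conventional medium on the f scale is f = 0.25, so f² = 0.25² = 0.0625 and d = 0.5. The conventional medium on the regression f² scale is 0.15, so d = 2√0.15 = 0.775. The stated 0.25 matches neither.

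**4. Power of the planned t-test.** Noncentral t with df = 2n − 2 and noncentrality d·√(n/2). With n = 40: df = 78, critical value 1.991.

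- d = 1.0: noncentrality 1.0 × √20 = 4.47, power 99.3%.
- d = 0.775: power 92.8%.
- d = 0.5: noncentrality 0.5 × √20 = 2.24, power 59.8%.

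With losses:

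| Analysed per group | Power at d = 0.5 | Power at d = 1.0 | d detectable with 80% power |
|---|---|---|---|
| 40 (no loss) | 59.8% | 99.3% | 0.63 |
| 36 (10% loss) | 55.3% | 98.7% | 0.67 |
| 32 (20% loss) | 50.4% | 97.6% | 0.71 |

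For comparison, 80% power at d = 0.5 needs 64 per group, 128 in total.

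**The case against.** The strongest reply is that the plan fixes the effect by number, not by label. At f² = 0.25 each planned t-test has 99.3% power with 80 analysed and still 97.6% with 64. A reader might infer from the mismatches that the stated 80% power is simply not delivered. The document does not support that without a condition: the shortfall appears only if *medium* means d = 0.5. On the regression-scale medium (d = 0.775) the power is 92.8%.

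A reader might also call f² = 0.25 a large effect. That holds on the f scale, where 0.50 exceeds the conventional large value of 0.40. On the regression f² scale, 0.25 lies between medium (0.15) and large (0.35). What can be said is that it is not the medium value on either scale.

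The unstated number of response variables is no error in itself. A condensed article may leave it to the full protocol, and 11 responses fit within 80. Another route is possible too: a repeated-measures between-group test at f = 0.25, with an assumed four measures and correlation 0.5, needs 81. On that route the label would be right and only the exponent wrong. The document cannot settle this.

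Last, Phase 1 is a single cross-sectional assessment, so losses would come mainly from unusable scans or incomplete sessions, and the 10% and 20% rates are assumptions.

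These replies remove the unconditional power claim. They leave untouched the zero allowance, the disagreement between label and number, and the absence of any MANOVA from the analysis section.

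**Conclusion.** The paragraph is wrong as written on three counts.

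1. The attrition allowance is exactly zero, which contradicts the claim that losses are covered. This needs no assumption.
2. The label and the effect size disagree under both common conventions.
3. The 80% power belongs to no analysis that the article describes.

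The practical size of the problem is the gap between the two readings of the effect. For the planned test with 40 per group, power is 99.3% if the number is meant and 59.8% if a conventional medium d of 0.5 is meant. Whichever was intended, 80% is the power of this test at d = 0.63, and at d = 0.67 to 0.71 under the assumed losses. These figures assume equal groups, a single outcome, the t-test and the unadjusted two-sided 0.05 threshold in section 2.3.6.7.

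**What to change.** Keep N = 80 and rewrite section 2.3.5 for the planned test, for example: *With 40 participants per group analysed, a two-sided t-test at the 0.05 level has 80% power to detect a standardised difference of d = 0.63. If 10 to 20% of data are unusable, the detectable difference is d = 0.67 to 0.71.*

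Remove the medium label, the MANOVA basis and the statement that attrition is covered. Say that the loss rates are assumptions, or replace them with a rate the sponsor can support, and name the outcome to which the detectable difference refers. If the sponsor would rather keep 80 as the number evaluable, recruitment has to rise, to 89 at 10% loss or 100 at 20%.

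The cost of the first option is one paragraph and no extra participants. Its downside is that the stated sensitivity becomes less favourable than medium. The article says that no participant data had been collected at publication, so the correction can still be made before results are known.
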